### Randomisation

#### Sequence generation and concealment

Schools will be stratified by decile grouping and allocated unique identifiers. Within each of the three decile strata, schools will be randomly allocated to one of the two study arms (intervention or control) according to a computer-generated procedure coded by the trial statistician (fourth author), who will be unaware of the cluster identifiers. Allocation is to be revealed in three waves, after the recruitment of all participating schools is completed for a given school term. Provision for an arbitrary number of waves as needed has been made, in case recruitment is low.

#### Allocation and concealment

The randomisation scheme aims at maintaining balance within each decile stratum. The details of the scheme are otherwise withheld by the trial statistician until the end of data collection to uphold concealment. Once each school has nominated the students - and they have consented/assented to participate and been assessed for eligibility - the lead researcher will be informed of each cluster’s allocation. The lead researcher will then advise the school of the study arm to which they have been allocated, in order to facilitate logistical aspects of arranging times and venues for the intervention. Allocation will be concealed from individual participants until after completion of the baseline outcome measures.

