**Participant flow through the study.**

#### Primary outcome measure

The primary outcome for effectiveness of this intervention is the participant’s self-rating of anxiety symptoms as assessed with the Multidimensional Anxiety Scale for Children – Short form (MASC-10) (Table 
3). The measurement taken 9 weeks after baseline will be the primary endpoint. The MASC-10 is the most widely used measure of anxiety in research with children and its psychometric properties have been well researched. Test-retest reliability of the MASC-10 is moderate to excellent and it has good reported internal consistency (Baldwin & Dadds,
2007; March & Sullivan,
1999; Muris et al.,
1998). Birmaher et al. (
1997) have demonstrated good discriminant validity. The MASC-10 has strong discriminant validity supported by correlation with the CDI (Myers & Winters) and SCARED (Muris et al.,
1998); it is sensitive to treatment effects and able to discriminate between anxious children and non-anxious children (Myers & Winters,
2002).

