**Table 3 Tab3:** **Outcome measures**

Outcome measure	Rater	Instrument	Description
**Anxiety**	Child	Multidimensional Anxiety Scale for Children: Short form (MASC-10) (March, 1997)	Self-rated questionnaire with 10 items measuring the child’s thoughts and emotions, specifically related to anxiety.
	Parent	Revised Child Anxiety and Depression Scale – Parent report, short version (RCADS-PS) (Weiss & Chorpita, 2011)	Parent-report questionnaire with 25 items measuring their child’s anxiety and depression.
		Modification of original measure.	
	Teacher	School Anxiety Scale (SAS) (Lyneham et al., 2008)	Teacher-rated questionnaire with 16 items that measure the level of anxious behaviours a child is displaying.
**Depression**	Child	Children’s Depression Inventory – 2 (CDI-2) (Kovacs, 1992)	Self-rated scale with 10 items measuring the child’s mood, thoughts and presentation of depressive symptoms.
	Parent	Revised Child Anxiety and Depression Scale – Parent report, short version (RCADS-PS) (Weiss & Chorpita, 2011)	Described above.
		Modification of original measure.	
**Self-esteem**	Child	Rosenberg Self Esteem Scale (RSES) (Rosenberg, 1965).	Self-rated questionnaire with 10 items measuring the child’s thoughts about their own abilities and self-worth.
	Parent	Single Item Self-Esteem Scale (SISES) (Robins et al., 2001).	Single item parent-rated questionnaire that measures the parent’s general evaluation of the child’s self-esteem.
**Participation in daily occupations**	Child	Canadian Occupational Performance Measure (COPM) - modified (Law et al., 2005)	Measures self-reported ability to participate in daily activities and satisfaction with one’s ability to participate in those daily activities. Two chosen activities the individual would like to improve on from a menu of activities pertinent to the intervention goals.
	Parent	Canadian Occupational Performance Measure (COPM) - modified (Law et al., 2005)	Measures parent-report of their child’s ability to participate in the two daily activities chosen by their child (see above) and satisfaction with their child’s ability to participate in those daily activities.
**Life satisfaction and wellbeing**	Child	Wellbeing and life satisfaction questions (The Children’s Society, 2012)	Self-rated questionnaire with five items measuring a child’s sense of wellbeing and life satisfaction.

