### Blinding

Outcome measures will be taken at school by a research assistant blinded to the treatment allocation of each cluster. Two research assistants will be used to ensure they cannot guess study allocation by the number of times they have conducted testing at a school. Any inadvertent unblinding of the research assistant will be acknowledged in the final report.

Blinding of the lead researcher, who is facilitating the intervention; participants at the cluster level after screening; or the individual level after baseline measures are taken, will not be possible. This is due to the pragmatic trial design and the nature of the experimental intervention that will require active participation and interaction from participants compared to the control, which requires no involvement or participation. Blinding participants is notoriously difficult in complex and non-pharmacological interventions, by nature of them requiring significant participant interaction; the difficult is increased when the comparison group is a waitlist control group (Boutron et al.,
2004). An attention-control intervention was considered to counter-act this; however, including this is beyond the scope, budget and timeframe of this study.

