### Statistical analysis

A Repeated Measures Analysis of Covariance (RM-ANCOVA) analysis of the data will allow comparisons of between-subject (intervention versus waitlist control) and within-subject (repeated measures on outcomes) factors and their interactions, while statistically controlling for baseline scores, cluster’s decile rank and other potential covariates that may be identified as the result of the blind review (e.g. gender, individual’s score on screening instrument). Incorporating individual-level covariates is more efficient (statistically) than cluster-level covariates (Eldridge & Kerry,
2012). The two predetermined covariates specified for this study are:

Baseline scores on outcome measures;School decile;Time from baseline to assessment (treated as categorical data) for repeated measures analyses.

To maximise statistical efficiency, both post-intervention and follow-up measurements will be included in all regressions for a given outcome, with specific contrasts being used to isolate results at any time point. There is only one planned comparison for testing the primary hypothesis so no adjustment for multiplicity is required. Given the need to make multiple comparisons for the secondary hypotheses, False Discovery Rate control will be applied to protect against Type I errors (Benjamini & Hochberg,
1995).

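### Schools can learn their arm before baseline, and no rule keeps the teachers who rate the School Anxiety Scale unaware until their baseline ratings are done

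*Protocol article*

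**What the plan says.** The Allocation and concealment section sets the trigger for release. The lead researcher learns a school's arm once students have been nominated and "they have consented/assented to participate and been assessed for eligibility". Next, "The lead researcher will then advise the school of the study arm to which they have been allocated", and the reason given is the logistics of times and venues. The section then limits who is kept unaware: "Allocation will be concealed from individual participants until after completion of the baseline outcome measures".

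The Blinding section draws the same line. It says that blinding of "participants at the cluster level after screening; or the individual level after baseline measures are taken, will not be possible".

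Table 3 lists the School Anxiety Scale (SAS) as a "Teacher-rated questionnaire with 16 items that measure the level of anxious behaviours a child is displaying", and teacher-rated symptoms are part of the secondary hypotheses. The Statistical analysis section names "Baseline scores on outcome measures" among the predetermined covariates. The Blind review section defends adding further covariates late on the footing that they come from baseline data which allocation cannot have touched.

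**The concern.** A baseline covariate is safe to adjust for because it is fixed before anyone who supplies it can know the arm. Here the person who supplies the SAS baseline works at a school that may already have been told. A teacher who knows that the group will start this term, or that the school must wait, may rate the same child differently. If such shifts differ between arms, the covariate carries part of the allocation, and adjusting for it moves the estimated effect.

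Randomisation does not remove a shift of this kind, and False Discovery Rate control across the secondary outcomes does not correct bias. A review carried out without knowledge of arm could not see a difference between arms at baseline. What is at stake is the teacher-rated anxiety result, which is the one anxiety rating supplied by school staff.

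**Working it through.** No figure in the protocol bears on this point, so there is none to reproduce. The check is on the order of events, followed by the algebra of the bias.

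**Order of events**

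1. *Trigger.* Release depends on nomination, consent or assent, and eligibility (Allocation and concealment). Completion of baseline is not a condition.
2. *Who is told.* The lead researcher first, then the school.
3. *Who is shielded until baseline is complete.* Individual participants only. Schools and teachers are not named.
4. *Cross-check.* The Blinding section ends blinding at two different times: after screening for the cluster, and after baseline for the individual. If schools heard only after baseline, one time would have been enough.
5. *Are screening and baseline the same step?* It appears not. The Statistical analysis section mentions the score on a screening instrument as a possible extra covariate, separate from baseline scores.

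So the school can know its arm while baseline is still outstanding. This follows from two sections read together and is not stated in a single sentence.

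**Form of the bias**

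Let *b* be the slope of the post-intervention SAS on its baseline, and *s* the shift in baseline ratings in one arm relative to the other that knowledge of arm causes. With no true effect on the outcome,

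bias in the adjusted difference = −*b* × *s*.

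The sign is opposite to the shift. If teachers at intervention schools rate anxiety higher at baseline, the adjusted difference moves towards an apparent benefit. If teachers at waitlist schools do so, it moves the other way. The documents support neither direction.

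**Illustration only**

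The protocol gives neither *b* nor *s*. The values below are assumptions, and the results are in SD units of the SAS.

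| *b* | *s* = 0.1 | *s* = 0.2 | *s* = 0.3 |
|---|---|---|---|
| 0.4 | −0.04 | −0.08 | −0.12 |
| 0.5 | −0.05 | −0.10 | −0.15 |
| 0.6 | −0.06 | −0.12 | −0.18 |
| 0.7 | −0.07 | −0.14 | −0.21 |

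For the effect on a 5% two-sided test, take 63 children per arm (Sample size), equal SDs at both times so that the residual variance is 1 − *b*², and no clustering:

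- SE = √(2(1 − *b*²)/63), which is √(1.5/63) = 0.154 for *b* = 0.5 and √(1.02/63) = 0.127 for *b* = 0.7.
- With *d* = *b* × *s* / SE, the rejection rate under no true effect is P(Z > 1.96 − *d*) + P(Z < −1.96 − *d*).
- For *b* = 0.5 and *s* = 0.1, 0.2, 0.3, this gives 0.062, 0.099 and 0.163.
- For *b* = 0.7 and the same shifts, it gives 0.085, 0.196 and 0.379.

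Clustering would enlarge the SE, so the same bias would inflate the error rate by less than these figures.

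**The case against.** The strongest reply is that telling a school is not the same as telling its raters. The notice goes out for logistics, and the school contacts that the protocol describes are senior staff. No section says that the teachers who complete the SAS are told, or when they complete it. The Participants section uses teacher reports for exclusion, so some teacher information is gathered before release, and the participant-flow figure is not available. All of this stands. It means that the ratings *can* be influenced, not that they are. It does not close the gap, because the stated rule shields individual participants and nobody else.

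A second reply is that "Outcome measures will be taken at school by a research assistant blinded to the treatment allocation of each cluster". That blinds the collector. It does not blind a teacher who fills in the scale.

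A third is that teachers' post-intervention ratings will be unblinded whatever is done. That is true, and the fix protects only the baseline. But the later unblinding comes with the design, whereas this exposure is avoidable.

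A reader might go further and infer that the primary result is compromised. The documents do not support that. The primary outcome is the child's "self-rating of anxiety symptoms as assessed with the Multidimensional Anxiety Scale for Children", and children are to be kept unaware until baseline is done. It is exposed only if staff break that concealment. A reader might also suspect selection, or differential drop-out between disclosure and baseline. Nomination, consent and eligibility all precede release, and families are not to be told at that stage, so no mechanism for either is documented.

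**Conclusion.** The concern holds for the teacher-rated SAS baseline. The release rule allows a school to know its arm before that baseline is taken, and nothing stated keeps the rating teachers unaware. The premise in the Blind review section, that baseline data are unaffected by allocation, is therefore not secured for this measure. Parent ratings are exposed only indirectly, for instance if the school passes the information on.

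The size is unknown. The range of 0.04 to 0.21 SD rests wholly on the assumed slopes and shifts, and the error rates also ignore clustering. It would be tempting to express the bias as a share of the 5-point difference in the Sample size section, but that is a *t*-score threshold for the MASC-10. The documents give no target or SD for the SAS, so no such percentage can be justified.

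This is an avoidable weakness in a secondary outcome and worth correcting. It is not a threat to the primary comparison as the protocol describes it.

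**What to change.** Amend Allocation and concealment so that a school's arm goes to the lead researcher and the school only after the baseline measures there, teacher ratings included, have been collected. Set a cut-off date for outstanding forms so that one late questionnaire does not hold up the term. Schools can hold provisional times and venues in the meantime, which meets the logistical purpose of the early notice. Bring the cluster-level time in the Blinding section into line.

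If full deferral is impracticable, the minimum is to require rating teachers to complete the baseline SAS before the school is told, and to say so.

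The cost is a short delay in confirming rooms and times. The cut-off should be fitted to the school term, because the programme takes 8 weeks of it and the primary endpoint is 9 weeks after baseline.

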### Blinding

Outcome measures will be taken at school by a research assistant blinded to the treatment allocation of each cluster. Two research assistants will be used to ensure they cannot guess study allocation by the number of times they have conducted testing at a school. Any inadvertent unblinding of the research assistant will be acknowledged in the final report.

Blinding of the lead researcher, who is facilitating the intervention; participants at the cluster level after screening; or the individual level after baseline measures are taken, will not be possible. This is due to the pragmatic trial design and the nature of the experimental intervention that will require active participation and interaction from participants compared to the control, which requires no involvement or participation. Blinding participants is notoriously difficult in complex and non-pharmacological interventions, by nature of them requiring significant participant interaction; the difficult is increased when the comparison group is a waitlist control group (Boutron et al.,
2004). An attention-control intervention was considered to counter-act this; however, including this is beyond the scope, budget and timeframe of this study.

### Efficacy end points (EEP)

The primary EEP for this study will be one-week post-intervention on completion of the post-intervention primary outcome measure, the MASC-10. Secondary EEPs for this study will at the 8–9 week follow-up on completion of the primary outcome measure (MASC-10) and post-intervention and 8 week follow up completion of all other outcomes.

### Data management

Data will be entered into an Access database by a research assistant. Range and logic checks will be built in to assist with data cleaning. A data monitor will be assigned to review the quality and completeness of data collected. The data monitor will conduct an unblinded review of the data at two time points:

On completion of the first round of intervention and waitlist groups being implemented (mid-July, 2014).On completion of the first year of the trial (January-February 2015).

This review will have the scope to inform recommendations about data quality and collection, data completeness, potential changes to the sample size and to review the adverse event log for safety issues. The lead researcher and trial statistician involved in randomisation will remain blinded to the data to prevent potential bias in intervention delivery and the blind review. No stopping rules are in place.

### Statistical analysis plan

Data will be analysed using the Statistical Package for the Social Sciences (SPSS version 20), SAS version 9.4 and R version 3.1.

### Descriptive statistics

Means, standard deviations and frequencies will be used to describe demographic, screening and outcome variables at both the cluster and the individual level. Analysis of descriptive statistics will also allow variables to be checked for any violations of assumptions underpinning the statistical techniques planned, such as checking for normality, outliers, and missing data.

### Sets for analysis

As a pragmatic trial this study will utilise an Intention-to-Treat (ITT) approach to analysis to reduce the potential for upward bias in the estimated effect size (Eldridge & Kerry,
2012). The Primary ITT data set will consist of all data from the parallel trial with participants randomised to one of the two study arms, i.e. intervention or waitlist control. Treatment allocation for this data set will be the allocated treatment at randomisation regardless of treatment received. The Secondary ITT data set will consist of all data from the Primary ITT group, plus the additional data from the crossover group (those originally allocated to the control group in the parallel trial) who go on to receive the intervention also. Treatment allocation for the Per Protocol (PP) data set will be the actual treatment received. Other major protocol violators will be removed from the PP data set.

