**Methods/design:**

In this two-arm, pragmatic, cluster-randomised controlled trial, 154 children will be recruited from 14 schools. All mainstream schools in the region will be eligible and a convenience sample of 14 schools, stratified by decile ranking (i.e. low, medium, and high) will be recruited. Eight to twelve students aged 11–13 years from each school will be recruited by senior school personnel. Following consent, schools will be randomised to either the intervention or waitlist control arm of the trial. The study will employ a parallel and one-way waitlist-to-intervention crossover design. Each cluster’s involvement will last up to 19 or 31 weeks depending on allocation to the intervention or waitlist respectively. The primary outcome is symptoms of anxiety and secondary outcomes are symptoms of depression, self-esteem, participation in daily occupations and wellbeing. Outcome measurement will be repeated at baseline, post-intervention and again at 8–9 weeks follow-up. Planned statistical analyses will utilise repeated measures analysis of covariance. The primary analysis will be based on an intention-to-treat analysis set and include only parallel data. The crossover data will only be used in secondary analyses.

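### Two supportive analysis sets are wrongly defined: the Secondary ITT set pools one-way crossover data that have no randomised control, and the Per Protocol set is an as-treated set

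*Protocol article*

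**What the plan says.** The Protocol article defines three sets under Sets for analysis.

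- **Primary ITT.** "The Primary ITT data set will consist of all data from the parallel trial with participants randomised to one of the two study arms", with this labelling rule: "Treatment allocation for this data set will be the allocated treatment at randomisation regardless of treatment received".
- **Secondary ITT.** "The Secondary ITT data set will consist of all data from the Primary ITT group, plus the additional data from the crossover group", meaning the children first allocated to the waitlist who later receive the intervention.
- **Per Protocol.** "Treatment allocation for the Per Protocol (PP) data set will be the actual treatment received". The next sentence adds: "Other major protocol violators will be removed from the PP data set".

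The Abstract (Methods/design) fixes their roles: "The primary analysis will be based on an intention-to-treat analysis set and include only parallel data", and "The crossover data will only be used in secondary analyses".

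Trial design describes the crossover as one-way, from waitlist to intervention. Statistical analysis lists the prespecified covariates as baseline score, school decile and "Time from baseline to assessment (treated as categorical data) for repeated measures analyses". It names no calendar-term or study-period effect, and the article gives no separate model for the pooled set.

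**The concern.** Randomisation protects one contrast: intervention schools against waitlist schools during the parallel part. Once the waitlist schools switch, all their children are treated and no randomised school stays untreated beside them. Adding those data under the name ITT suggests a protection that the added comparison does not have.

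The Per Protocol rule has a different fault. Labelling children by treatment received moves them between arms. That is an as-treated analysis. A per-protocol set normally keeps children in their allocated arm and drops those who departed from it.

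What is at stake is the reading of secondary results. A pooled estimate would look more precise than the primary one while carrying a bias that its label hides. A result called per protocol would mix allocation with attendance. Sets for analysis adopts ITT in order to limit upward bias in the effect estimate, and these two definitions work against that aim.

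**Working it through.** **1. Does the plan's own sample size rely on crossover data?** Inputs from Sample size: difference 5 T-score points, 80% power, 5% level (two-sided assumed), design effect 0.98. No SD is stated; I assume 10. The t-test calculation gives 63.8, so 64 per arm. Then 64 × 0.98 = 62.7, so 63 per arm and 126 in total, as stated. Only the parallel comparison enters.

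**2. Can the named time term separate treatment from time?** The Abstract gives involvement of up to 19 weeks (intervention) or 31 weeks (waitlist), so the waitlist runs 31 − 19 = 12 weeks longer. The primary endpoint is 9 weeks after baseline.

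- *Clock runs from the original baseline.* The waitlist's own post-intervention visit falls at about 9 + 12 = 21 weeks, beyond the intervention arm's last visit. That time category holds only treated waitlist children. Treatment is aliased with time, and the data add nothing to the effect.
- *Clock restarts at crossover.* The data do contribute, but through a before-after contrast within the waitlist. With no period term, this absorbs term, maturation and repeat-testing effects. It also absorbs regression to the mean, since Participants has staff nominating children for early symptoms.

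**3. How much weight would the before-after contrast take?** Let I1 and C1 be the arm means after the parallel part, C2 the waitlist mean after its own course, and c the correlation of C1 and C2. Assume equal variances and no period effect in the model. The pooled estimate is b(C2 − C1) + (1 − b)(I1 − C1), with variance proportional to b² + (1 − b)² + 1 − 2bc. Setting the derivative to zero gives b = (1 + c)/2.

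**4. Size for an assumed 2-point drift.** Assume equal correlation ρ = 0.4 to 0.7 between any two visits, an ANCOVA slope equal to ρ, and no clustering. None of these values is in the article.

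| Analysis | c | b | Shift in C2 left after adjustment | Bias (points) |
|---|---|---|---|---|
| Re-baselined; drift shifts the new baseline and the outcome alike | ρ(1 − ρ)/(1 + ρ) = 0.17 to 0.12 | 0.59 to 0.56 | 2(1 − ρ) = 1.2 to 0.6 | 0.70 to 0.34 |
| Re-baselined; drift confined to the crossover course | as above | 0.59 to 0.56 | 2 | 1.2 to 1.1 |
| Original baseline only | ρ/(1 + ρ) = 0.29 to 0.41 | 0.64 to 0.71 | 2 | 1.3 to 1.4 |

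The first row is 7% to 14% of the 5-point target (0.34/5 and 0.70/5).

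**5. Cross-check with simple equal-weight pooling.** Take 63 parallel-treated plus 63 crossover-treated children against 63 controls, zero true effect, residual SD 10 × √0.98 = 9.9, no re-baselining and clustering ignored. The bias is half the drift, so 1.0 point for a 2-point drift. The SE is 1.53 (within-child correlation 0) or 1.25 (correlation 0.5). The nominal 5% false-positive rate becomes 10% or 13%.

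**6. Per Protocol wording.** The two sentences are read together. Treatment is the treatment received, and *other* major violators are removed. The word *other* implies that children whose treatment differed from their allocation are violators too, yet they are kept and relabelled. Treatment fidelity records attendance, so non-attenders will be identifiable. On the plain reading, an intervention-arm child who attended nothing could be counted as a control.

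**The case against.** **The main result is not at risk.** This stands in full. The Abstract and Sets for analysis both restrict the primary analysis to parallel data as randomised. A reader might infer from the two definitions that the trial's randomised comparison is broken; the documents do not support that.

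**The waitlist is probably re-baselined.** Outcome measures gives the waitlist five assessments, and Waitlist-control places two of them in the parallel part. That leaves three, which matches a new baseline, post-intervention and follow-up. The participant-flow figure is not shown, so this is an inference, but a reasonable one. A reader might compare raw means instead and put 70% to 85% of the weight (c = 0.4 to 0.7) on the before-after contrast, or 72% to 93% with school clustering modelled. A 2-point fall would then give 1.4 to 1.9 points of spurious benefit, 28% to 37% of the target. That reading ignores the baseline adjustment named in Statistical analysis and should not be relied on.

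**The sign is open.** Background reports that symptoms in control groups typically increased, which would bias against the intervention. Regression to the mean may also have largely run its course during the waiting period, with the same effect.

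**Some calendar overlap may exist.** Allocation is revealed in three waves, over several terms. Early crossover schools may coincide with later waitlist schools, so saying that there is no concurrent control of any kind goes too far. But that overlap is not a randomised comparison, may be absent for the last wave, and cannot be used by a model without a calendar term.

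**Details may sit elsewhere.** Blind review may add covariates or choose another model, and a fuller plan may exist. That could improve the model. It does not change the set definitions, which the article states outright.

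**Any per-protocol set carries selection.** True, including the one proposed below. The avoidable fault is moving children between arms under a name that implies otherwise.

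**Conclusion.** The point holds for the two supportive sets and no further. The Secondary ITT set adds a non-randomised comparison under an ITT label, and the only time term named does not repair it: on one reading the added data are uninformative, on the other they are confounded. The Per Protocol set is an as-treated set by definition.

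Neither the direction nor the size of the pooling bias can be fixed from the documents. For an assumed 2-point drift with correlations of 0.4 to 0.7 and no clustering, it is about 0.3 to 0.7 T-score points if children are re-baselined and the drift shifts the new baseline and the outcome alike. It exceeds 1 point if they are not, or if the drift falls wholly within the crossover course. The article gives no figures from which to size the Per Protocol fault.

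**What to change.** - Do not pool crossover data into any set labelled ITT. Report the waitlist's change over its own intervention period separately, as an uncontrolled, non-randomised estimate on which no confirmatory claim rests.
- Define Per Protocol as children who adhered to their allocated arm. Exclude violators and never re-assign them. Describe the set as supportive, because it still carries selection by adherence.
- Optionally, if the effect of treatment received is of interest, estimate a complier-average effect with randomised arm as the instrument.

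The change is to wording in the analysis plan. It gives up the apparent precision from the crossover data. The 63 per arm never depended on those data, so power for the primary comparison is unchanged.
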